## 8.7 Dosage modifications

In an event when the administration of 30 vials is not practical, doses may drop to 20 or 10 vials, depending on feasibility. In the event clear efficacy is observed in cohort 1, doses may drop below 10 vials or dosing times may be reduced.

Progression and dosing modifications of subsequent cohorts will be decided by teleconference of the trial steering committee. Any safety concerns would be referred to the independent DSMB on completion of dosing of each cohort of 3 patients + 24 hours to enable collection of physiological outcomes.

The DSMB will actively monitor emerging safety and efficacy data to make recommendations about early study closure or the initiation of a larger randomised controlled clinical trial.

The dose administered cannot be modified due to patient / personal legal representative request.

Given the severity of the illness in ventilated Covid-19 patients, safety data will be interpreted with caution and will not be formally compared between active intervention and control groups.

- Dosing will be stopped in individual patients upon persistent deterioration of oxygenation during or after surfactant administration
- Study stopping rules for futility or efficacy are provided in the statistical analysis section.
- The protocol team will review emerging AE/SAE/SADEs data daily. If 3 or more patients develop the same SAE after administration of study drug, the study will be paused pending review by the DSMB. The study may also pause at the discretion of the Principal Investigator if there are a significant number of unexpected AEs/SAEs/SADEs and referred to the DSMB for review.
- The DSMB will formally review the safety data after every three subjects and is available for ad hoc reviews for other safety concerns as noted above.

## 8.8 Known drug reactions and interaction with other therapies

None known.

## 8.9 Concomitant medication

Concomitant medication administered as part of routine clinical care whilst the patient is hospitalised will be recorded in the eCRF. This data will be available in the patients' medical records. No routine concomitant medications will be withheld as a result of participation in this study.

## 8.10 Trial restrictions

There are no restrictions in relation to dietary requirements or contraception in this study. Patients will be hospitalised, and their care will be managed by the direct clinical care team in the intensive care unit.

## 8.11 Assessment of compliance with treatment

Compliance will be assessed by the investigator or delegate as part of the clinical monitoring required for the study (as shown in the schedule of events, appendix 1). Vital signs and ventilator parameters will be reviewed on an ongoing basis. Non-compliance with treatment will be recorded in the eCRF and patient medical notes. Non-compliance resulting in an AE, SAE or SUSAR will be recorded and

reported according to the information outlined in section 9.3. Follow up of non-compliance related adverse reactions will be carried out in line with section 9.9.

## 9 PHARMACOVIGILANCE

### 9.1 Definitions

The following definitions have been adapted from Directive 2001/20/EC, ICH-GCP E6 (r2), Directive 93/42/EC, ISO 14155: 2011 and MEDDEV 2.7/3:

| Term                                                 | Definition                                                                                                                                                                                                                                                                                                                                                                                                                                                                                                                                                                                                                                                                                                                                                                                                                                                                                   |
|------------------------------------------------------|----------------------------------------------------------------------------------------------------------------------------------------------------------------------------------------------------------------------------------------------------------------------------------------------------------------------------------------------------------------------------------------------------------------------------------------------------------------------------------------------------------------------------------------------------------------------------------------------------------------------------------------------------------------------------------------------------------------------------------------------------------------------------------------------------------------------------------------------------------------------------------------------|
| Adverse Event (AE)                            | Any untoward medical occurrence in a participant to whom a medicinal product has been administered, including occurrences which are not necessarily caused by or related to that product.                                                                                                                                                                                                                                                                                                                                                                                                                                                                                                                                                                                                                                                                                                    |
| Adverse Reaction (AR)                         | 
An untoward and unintended response in a participant to an investigational medicinal product which is related to any dose administered to that participant.
 
The phrase "response to an investigational medicinal product" means that a causal relationship between a trial medication and an AE is at least a reasonable possibility, i.e. the relationship cannot be ruled out.
 
All cases judged by either the reporting medically qualified professional or the Sponsor as having a reasonable suspected causal relationship to the trial medication qualify as adverse reactions. It is important to note that this is entirely separate to the known side effects listed in the SmPC. It is specifically a temporal relationship between taking the drug, the half-life, and the time of the event or any valid alternative aetiology that would explain the event.
 |
| Serious Adverse Event (SAE)                   | 
A serious adverse event is any untoward medical occurrence that:
 
 
• results in death
 
• is life-threatening
 
• requires inpatient hospitalisation or prolongation of existing hospitalisation
 
• results in persistent or significant disability/incapacity
 
• consists of a congenital anomaly or birth defect
 
 
Other 'important medical events' may also be considered serious if they jeopardise the participant or require an intervention to prevent one of the above consequences.
 
NOTE: The term "life-threatening" in the definition of "serious" refers to an event in which the participant was at risk of death at the time of the event; it does not refer to an event which hypothetically might have caused death if it were more severe.
                                 |
| Serious Adverse Reaction (SAR)                | An adverse event that is both serious and, in the opinion of the reporting Investigator, believed with reasonable probability to be due to one of the trial treatments, based on the information provided.                                                                                                                                                                                                                                                                                                                                                                                                                                                                                                                                                                                                                                                                                   |
| Suspected Unexpected Serious Adverse Reaction | A serious adverse reaction, the nature and severity of which is not consistent with the information about the medicinal product in                                                                                                                                                                                                                                                                                                                                                                                                                                                                                                                                                                                                                                                                                                                                                           |

|                                                            |                                                                                                                                                                                                                                                                                                                                                                                                                                                                                                                                                                           |
|------------------------------------------------------------|---------------------------------------------------------------------------------------------------------------------------------------------------------------------------------------------------------------------------------------------------------------------------------------------------------------------------------------------------------------------------------------------------------------------------------------------------------------------------------------------------------------------------------------------------------------------------|
| (SUSAR)                                             | 
question set out in the reference safety information:
 
 
in the case of a product with a marketing authorisation, this could be in the summary of product characteristics (SmPC) for that product, so long as it is being used within its licence. If it is being used off label an assessment of the SmPCs suitability will need to be undertaken.
 
in the case of any other investigational medicinal product, in the investigator's brochure (IB) relating to the trial in question
 
                      |
| Adverse Event (AE)-(device)                         | 
Any untoward medical occurrence, unintended disease or injury, or untoward clinical signs (including abnormal laboratory findings) in subjects, users or other persons, whether or not related to the investigational medical device
 
NOTE 1 This definition includes events related to the investigational medical device or the comparator.
 
NOTE 2 This definition includes events related to the procedures involved.
 
NOTE 3 For users or other persons, this definition is restricted to events related to investigational medical devices
 |
| Adverse Device Effect (ADE)                         | 
Adverse event related to the use of an investigational medical device.
 
NOTE 1 This definition includes adverse events resulting from insufficient or inadequate instructions for use, deployment, implantation, installation, or operation, or any malfunction of the investigational medical device.
 
NOTE 2 This definition includes any event resulting from use error or from intentional misuse of the investigational medical device.
                                                                                                           |
| Serious Adverse Device Effect (SADE)                | Adverse device effect that has resulted in any of the consequences characteristic of a serious adverse event.                                                                                                                                                                                                                                                                                                                                                                                                                                                             |
| Anticipated Serious Adverse Device Effect (ASADE)   | Anticipated serious adverse device effect (ASADE) is an effect which by its nature, incidence, severity or outcome has been identified in the risk analysis report or Investigator's Brochure.                                                                                                                                                                                                                                                                                                                                                                            |
| Unanticipated Serious Adverse Device Effect (USADE) | Serious adverse device effect which by its nature, incidence, severity or outcome has not been identified in the current version of the risk analysis report or Investigator's Brochure.                                                                                                                                                                                                                                                                                                                                                                                  |
| Device Deficiency (DD)                              | 
Inadequacy of a medical device with respect to its identity, quality, durability, reliability, safety or performance
 
NOTE Device deficiencies include malfunctions, use errors, and inadequate labelling
                                                                                                                                                                                                                                                                                                                                                    |

NB: to avoid confusion or misunderstanding of the difference between the terms "serious" and "severe", the following note of clarification is provided: "Severe" is often used to describe intensity of a specific event, which may be of relatively minor medical significance. "Seriousness" is the regulatory definition supplied above.

## 9.2 Operational definitions for (S)AEs/(S)ADEs

AEs, SAEs, SUSARs, ADEs, SADEs and USADEs will be recorded and reported according to applicable trial regulations.

All adverse events that occur between informed consent and until 28 days post cessation of trial treatment must be recorded in the subject notes and in the trial CRFs.

Pre-existing conditions (as recorded at screening visit) do not qualify as adverse events unless, in the opinion of the treating clinician, have worsened since baseline.

The following pre-specified respiratory deteriorations or adverse events occurring during nebulisation and occurring within 48 hours will be recorded:

1. Increase in oxygen or ventilator requirements [increase in  $FiO_2 \geq 0.2$  or more and or increase in PEEP of  $\geq 5$  or more to maintain the targeted oxygen saturation
2. Sustained deterioration in pulmonary ventilation variables  $>10\%$  (increase in peak or mean airway pressures, decrease in tidal volume)
3. Any episodes of new cardiac arrhythmia
4. Sustained reduction in mean arterial blood pressure (MAP) of  $>10\%$  or an increase in the vasopressor dose of Norepinephrine (0.1 mcg/kg/min), Epinephrine (0.1 mcg/kg/min) or the use of additional use of other inotropes (dopamine/dobutamine/milrinone) or vasopressors (vasopressin, terlipressin, phenylephrine)
5. Sustained increase in heart rate  $>20\%$
6. New bronchospasm requiring treatment

Other respiratory deteriorations: Incidence of pneumothorax (evidence on imaging), pulmonary haemorrhage (clinical), acute lobar collapse (evidence on imaging).

All SAEs and Device Deficiencies (as per definitions) must be recorded and reported to the Sponsor ([[contact]](mailto:[contact])) and CRO ([[contact]](mailto:[contact])) immediately/within 24hrs of the site becoming aware of the event.

### 9.3 Evaluation of Adverse Events

When an Adverse Event occurs, the investigator (PI or delegated clinician) is responsible for reviewing documentation related to the event. The investigator will record all relevant information on the eCRF and make an assessment on seriousness, causality and severity.

#### 9.3.1 Assessment of Severity

The PI or delegated clinician must perform an assessment of severity for each AE according to the following categories.

| Severity category     | Definition of severity category                                                                                               |
|-----------------------|-------------------------------------------------------------------------------------------------------------------------------|
| Mild
(Grade 1)     | AE that is easily tolerated by the trial participant, causing minimal discomfort and not interfering with everyday activities |
| Moderate
(Grade 2) | AE that is sufficiently discomforting to interfere with normal everyday activities                                            |

|                     |                                             |
|---------------------|---------------------------------------------|
| Severe
(Grade 3) | AE that prevents normal everyday activities |
|---------------------|---------------------------------------------|

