#### 3.3.2 Secondary Endpoints

The key secondary endpoint is safety over the first 28 days after administration of surfactant assessed by:

1. Cumulative incidence of serious adverse events (SAEs and SADEs);  
Cumulative incidence of Grade 3 and 4 adverse events (AEs)  
Cumulative incidence of ADEs and  
Changes in white cell count, hemoglobin, platelets, creatinine, glucose, total bilirubin, ALT, and AST over time.

Other secondary endpoints are:

2. Change in  $\text{PaO}_2/\text{FiO}_2$  at 24 and 48 hours after study initiation
3. Change in value of Ventilation Index at 24 and 48 hours after study initiation
4. Change in pulmonary compliance ( $\text{L}/\text{cmH}_2\text{O}$ ) at 24 and 48 hours after study initiation

5. Change in PEEP requirement at 24 and 48 hours after study initiation
6. Ordinal outcome assessed daily while hospitalised and on days 15 and 28
  1. *Not hospitalised, no limitations on activities*
  2. *Not hospitalised, limitation on activities;*
  3. *Hospitalised, not requiring supplemental oxygen;*
  4. *Hospitalised, requiring supplemental oxygen;*
  5. *Hospitalised, on non-invasive ventilation or high flow oxygen devices;*
  6. *Hospitalised, on invasive mechanical ventilation or ECMO;*
  7. *Death.*
7. Duration of mechanical ventilation- Number of days on mechanical ventilation
8. Mechanical ventilator free days (VFD) at day 21
9. Length of intensive care unit stay
10. Number of days hospitalised
11. Mortality at day 28 - Date and cause of death (if applicable)

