## 6 PARTICIPANT ELIGIBILITY CRITERIA

### 6.1 Inclusion criteria

1. Age  $\geq 18$  years old
2. Confirmed COVID-19 positive by PCR
3. Within 24 hours of mechanical ventilation
4. Assent obtained from personnel legal representative (PerLR) or professional legal representative (ProfLR)

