### **7.2 Consent**

It is the responsibility of the Principal Investigator or co-investigator (where the responsibility has been delegated by the Principal Investigator as captured on the Site Signature and Delegation Log) to obtain informed consent/eConsent for each patient before performing any trial related procedure.

It is not expected that patients considered for enrollment in this study will have the capacity to consent to take part due to the nature of the underlying disease process, as they will be under sedation and will be mechanically ventilated. As a result of this, the study information sheet will be made available to a personal legal representative (PerLR);

The personal legal representative will be fully informed of all aspects of the trial and the potential risks. The following will be emphasised:

- Participation in the study is entirely voluntary.
- Refusal to participate involves no penalty or loss of medical benefits.
- The patient may withdraw from the study at any time.
- The personal legal representative is free to ask questions at any time to allow him or her to understand the purpose of the study and the procedures involved.
- There may be no direct benefit from participation.

- The aims of the study and all tests to be carried out will be explained. The personal legal representative will be given the opportunity to ask about details of the trial and will then have time to consider whether to participate or not.
- The risks of participating in the study will be fully explained.

If the personal legal representative decides that they wish for the patient to participate, they will sign and date the legal representative declaration form and will be given a copy. The original legal representative declaration form will be stored as source documentation. These forms will also be signed and dated by the Investigator.

In cases where it is not possible for a personal legal representative to be present in the hospital due to local visitor restrictions, the study can be discussed with the patient's personal legal representative over the telephone. A copy of the legal representative declaration form can be sent to the personal legal representative via email or online declaration form and returned to the study team.

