## 8.7 Dosage schedules

Sequential vials of 108 mg Alveofact® in 2.2 mL buffer will be administered by nebulizer at 5-minute intervals with observation of vital signs, changes in oxygen saturation, FiO2 and Mean Airway Pressure. After each administration, 2 drops of normal saline will be nebulized, and the next vial administered. After administration of the first dose, dosing of Alveofact® will pause and vital signs and ventilation parameters will be assessed over the next 8 hours. If no grade 3 or grade 4 adverse events attributable to surfactant administration occur, another dose of Alveofact® will be administered and vital signs and ventilation parameters will be assessed over the next 16 hours. Again, if no grade 3 or grade 4 adverse events attributable to surfactant administration occur; a final dose of Alveofact® will be administered.

The dosing schedule for each group is displayed in the table below.

| Group | 0 Hours           | 8 Hours           | 24 Hours          |
|-------|-------------------|-------------------|-------------------|
| 1     | 10 x 108 mg vials | 10 x 108 mg vials | 10 x 108 mg vials |
| 2     | 10 x 108 mg vials | 10 x 108 mg vials | 30 x 108 mg vials |
| 3     | 10 x 108 mg vials | 30 x 108 mg vials | 30 x 108 mg vials |
| 4     | 30 x 108 mg vials | 30 x 108 mg vials | 30 x 108 mg vials |

If a dose time point is missed it should be administered as soon as it is possible. The investigator or delegate will assess the clinical stability of the patient prior to administering the dose or following a time point being missed or treatment being suspended.

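### The mandatory severity scale in 9.3.1 cannot separate Grade 2 from Grade 3 in sedated, ventilated patients, yet 8.7 makes that line one condition for doses 2 and 3

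*Protocol*

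**What the plan says.** Section 9.3.1 states that the investigator or delegated clinician "must perform an assessment of severity for each AE according to the following categories". The categories run on tolerability, discomfort and daily function. Grade 2 is an "AE that is sufficiently discomforting to interfere with normal everyday activities" and Grade 3 is an "AE that prevents normal everyday activities". No other grading scale is named anywhere in the protocol.

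Patients enter "Within 24 hours of mechanical ventilation" (Section 6.1). Section 7.2 does not expect them to have capacity to consent, because "they will be under sedation and will be mechanically ventilated". Treated patients are dosed at 0, 8 and 24 hours.

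Section 8.7 (Dosage schedules) uses the grade to release each further dose. "If no grade 3 or grade 4 adverse events attributable to surfactant administration occur", the second dose is given after 8 hours of observation, and the same condition applies to the third after a further 16 hours. The Grade 3 and 4 incidence is also part of the key secondary safety endpoint (Section 3.3.2), and Section 10 summarises it over the first 24 hours and over the whole study.

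Section 9.2 lists events to be recorded during nebulisation and within 48 hours. Most carry a physiological or treatment criterion. They are to be recorded; none is tied to a grade.

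**The concern.** A severity scale exists to give clinical judgement something observable to work from. Sedation and ventilation have already removed everyday activities before any adverse event occurs, and a sedated patient does not report discomfort. Read literally, the difference between interfering with and preventing everyday activities has nothing to attach to at the 8-hour and 24-hour decisions.

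Take a new arrhythmia, a vasopressor increase or treated bronchospasm that is attributed to surfactant. One investigator could call it Grade 2 and another Grade 3, and both would be following 9.3.1. If no other control is used, one patient would get the next dose and the other would not. The next dose can also be three times the previous one: in cohort 2 the third dose goes from 10 to 30 vials, and in cohort 3 the second dose does. Sections 2.1.2 and 9.3.4 state that there is no clinical experience with the combination product, so this per-patient check is worth having in working order.

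**Working it through.** There is no protocol figure to reproduce, because the point concerns a definition and the rule that uses it. The check sets the texts side by side and then bounds the size.

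**1. Does the scale have content in the dosing window?**
- Grade 2 criterion (9.3.1): discomfort interfering with everyday activities. Under sedation there is no report of discomfort and no everyday activity to interfere with.
- Grade 3 criterion (9.3.1): everyday activities prevented. This is already true of every participant at baseline.
- Result: neither criterion separates one event from another between 0 and 24 hours. The scale may become usable after recovery, but both dosing decisions fall before then.

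**2. Does another section supply the missing criterion?** Section 9.2 comes closest. Its six numbered items are:
1. A rise in FiO2 of at least 0.2 and/or in PEEP of at least 5 to hold the target saturation: an oxygenation measure.
2. Sustained worsening of more than 10% in airway pressures or tidal volume: no oxygenation measure.
3. "Any episodes of new cardiac arrhythmia": no oxygenation measure.
4. A sustained fall in mean arterial pressure of more than 10%, or a vasopressor or inotrope increase: no oxygenation measure.
5. A sustained heart-rate rise of more than 20%: no oxygenation measure.
6. New bronchospasm needing treatment: no oxygenation measure.

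None is mapped to a grade. Five of the six (items 2 to 6) also lie outside the individual oxygenation stop in 8.7 (Dosage modifications).

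Pneumothorax and pulmonary haemorrhage, listed separately in 9.2, are poor examples of the gap, since Section 6.2 names them as contraindications to surfactant.

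**3. How many decisions use the grade?**
- Treated patients (Section 4): 4 cohorts × 3 = 12.
- Graded checks per patient (8.7): 2, one before dose 2 and one before dose 3.
- Maximum: 12 × 2 = 24.

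The grade matters only at a check where an attributable event of disputable grade has occurred. The protocol gives no rate for such events.

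**4. Effect on the descriptive incidence.**
- One treated patient moved across the line: 1/12 = 8.3 percentage points.
- One control moved: 1/8 = 12.5 percentage points (controls: 4 × 2 = 8).
- For scale, with assumed counts and exact (Clopper-Pearson) 95% intervals: 2/12 = 16.7% (2.1% to 48.4%); 3/12 = 25.0% (5.5% to 57.2%).

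The shift from one regraded patient is small beside either interval, so the dosing check is the more important consequence.

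**The case against.** The strongest reply is that grade is only one of several conditions on the next dose. The event must also be attributed to surfactant. Section 8.7 (Dosage schedules) calls for an assessment of clinical stability before dosing. Section 8.7 (Dosage modifications) stops dosing on persistent deterioration of oxygenation, has AE data reviewed daily, pauses the study if three or more patients develop the same SAE, lets the Principal Investigator pause it, and provides for DSMB review. Section 4 lets investigators reduce the dose for adverse events of concern, although its context is mainly cohort decisions. Section 7.10 allows withdrawal for a safety event. SAEs are defined by outcome and reported within 24 hours whatever their grade (9.1, 9.2, 9.4). Severity is in any case left to medical judgement (9.4, Responsibilities), and safety is not to be formally compared between groups.

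Most of this stands, and it narrows the point. A reader might infer that the grade alone determines doses 2 and 3; the documents do not support that, because a Grade 2 label does not oblige anyone to dose an unstable patient. A reader might also want a probability of a wrong dosing decision; without an event rate, any such figure would be invented.

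What these controls do not do is repair the rule. The stability check and the oxygenation stop carry no threshold, and the stop covers oxygenation only. The SAE pause turns on seriousness, which Section 9.1 distinguishes from severity. DSMB review is scheduled after every three subjects, so, apart from ad hoc review, it does not settle an individual's 8-hour or 24-hour dose. A better scale would not remove judgement, but it would give judgement a criterion.

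**Conclusion.** The point holds as a defect in a stated rule. In the 0 to 24 hour window the compulsory scale gives no usable line between Grade 2 and Grade 3, and that line is one explicit condition for doses 2 and 3 as well as the definition of the Grade 3/4 safety component. The residual exposure is mainly non-serious, surfactant-attributed events outside oxygenation, in patients judged stable enough to dose, across at most 24 checks. This assumes that patients are sedated during dosing, as Section 7.2 expects, and that all 12 planned patients are treated.

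The effect on the safety endpoint is secondary: 8.3 or 12.5 points per regraded patient, in a descriptive summary with very wide intervals.

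A reader might also treat the absence of a Grade 4 definition as a fault in itself. The table as available ends at Grade 3, but it is split across pages in the text at hand, so a lost row cannot be ruled out. Grades 3 and 4 are always used together, so nothing here depends on it.

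This should be fixed, but other controls mean that it does not leave patients unprotected.

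**What to change.** Replace the 9.3.1 definitions with grades based on physiology or on the intervention needed. The most direct route is a table in 9.3.1 that maps each event listed in 9.2 to a grade, with thresholds set by the sponsor's clinicians and an intervention-based default for unlisted events. A published scale with such anchors would also serve. Grade each event as worsening from the pre-dose state, because every participant starts on ventilator support and would otherwise meet some criteria at baseline. Define Grade 4 if the source table has no such row. Then word the condition in 8.7 as *Grade 3 or higher on the 9.3.1 scale*.

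The cost is protocol and eCRF wording and brief site retraining. The 9.2 events are already recorded, so mapping them needs no extra data collection. The thresholds need clinical thought: some 9.2 triggers are modest, and setting all of them at Grade 3 could withhold doses unnecessarily.

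Under Section 13.10 the sponsor decides whether the amendment is substantial. If it is, a response is due within 35 days. The planned June to September 2020 period is 30 + 31 + 31 + 30 = 122 days, so that is 35/122 = 28.7% of it. The change is best made before enrolment or together with another amendment.
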